## Abstract

**Background:**

Chronic diseases, such as chronic obstructive pulmonary disease (COPD), asthma, type 2 diabetes, and heart failure, often coexist and contribute to a significant burden on individuals and health systems. The Assessment of Burden of Chronic Conditions (ABCC) tool, already in routine clinical use in the Netherlands, aims to comprehensively assess and visualize disease burden, stimulate self-management, and encourage shared decision-making. This study aims to validate the German and Italian versions of the ABCC tool and evaluate its effectiveness and cost-effectiveness in the South Tyrolean Primary Care setting.

**Methods:**

This is a cluster-randomized study involving approximately 400 patients with COPD, asthma, type 2 diabetes, and heart failure who received care from the South Tyrolean General Practices. Initially, the ABCC tool will be translated into German and Italian and validated. Subsequently, half of the participants will use the validated ABCC tool for patient-reported outcome measurement assessments, while the other half will receive usual care. The primary outcome measure is the change in the patients’ perception of the quality of care after 18 months. The secondary outcomes included changes in quality of life, self-management behavior, and healthcare utilization. The missing data will be managed using multiple imputations. Additionally, a cost-effectiveness analysis that considers the direct medical costs reimbursed by the National Health Service will be conducted.

**Discussion:**

This study provides insights into the application, validation, and efficacy of the ABCC tool in the South Tyrolean healthcare context. The tool’s potential to enhance person-centered care, improve the quality of life, and possibly reduce healthcare costs could greatly contribute to sustainable healthcare. The challenges of implementation, such as software integration and the use of an EU data platform, will provide lessons for future international patient care data management.

**Trial registration:**

ISRCTN registry, ISRCTN13531607. Registered on August 23, 2023.

**Supplementary Information:**

The online version contains supplementary material available at 10.1186/s13063-024-08041-9.

## Administrative information

Note: the numbers in curly brackets in this protocol refer to SPIRIT checklist item numbers. The order of the items has been modified to group similar items (see http://www.equator-network.org/reporting-guidelines/ spirit-2013-statement-defining-standard-protocol-itemsfor- clinical-trials/).

## Introduction

### Background and rationale {6a}

Chronic diseases pose a significant burden on healthcare systems globally [1]. This situation is similar to that in South Tyrol, Italy [2]. The complexity of chronic disease management often results in inefficient care, patient dissatisfaction, and increased healthcare costs [3]. Therefore, there is an urgent need for an effective and integrated care model for managing chronic diseases [4]. This has led to the emergence of the Chronic Care Model (CCM), which has been proven to provide better health outcomes for patients and improve efficiency in healthcare systems [5].

To enhance the effectiveness of CCM, the Assessment of Burden of Chronic Conditions (ABCC) tool has been developed [6]. This tool has been successfully implemented in the Netherlands, demonstrating its potential benefits in chronic disease management [7]. It is currently available through various providers, including hospital information systems and personal health environments [8]. However, its implementation in other regions, such as South Tyrol, has yet to be explored.

The ABCC tool promises to improve chronic care management by capturing and integrating patients’ comprehensive health information into a digital platform. This comprehensive approach may facilitate a more individualized and person-centered care plan, leading to improved health outcomes [7]. Furthermore, the integration of ABCC findings into an electronic health record (EHR) system ensures that information is secure, accurate, and accessible, thereby enhancing the delivery of care [9, 10].

Despite its potential benefits, the implementation of the ABCC tool in the CCM in South Tyrol presents several challenges. These include the adaptation of the tool to German and Italian languages, digitalization of the tool, validation of the tool on patients, study of its efficacy and cost-effectiveness in general practice, and integration into the electronic health record (EHR).

Through this project, we aim to contribute to the body of knowledge on integrated chronic care models and provide valuable insights into the use of digital tools in chronic disease management. Ultimately, the successful implementation of the ABCC tool could represent a significant step towards improving the quality of care for patients with chronic diseases in South Tyrol and beyond.

## Objectives {7}

The primary objective of this project is to evaluate the effectiveness of the Dutch ABCC tool adapted for the South Tyrol’s general practice settings. This evaluation will focus on determining the impact of the culturally translated and regionally validated ABCC instrument on patients with chronic diseases in South Tyrol. The key research question is, ‘‘How does the adapted ABCC tool affect perceived quality of care and the need for further health services in these patients, compared with usual care, after 18 months?” Should this adapted tool prove effective, our aim is to implement it in primary care and integrate its findings into electronic health records systems.

## Trial design {8}

This study is designed to explore the effectiveness and cost-effectiveness of the ABCC tool in primary care settings in Southern Tyrol. It will follow a pragmatic, cluster-randomized design, with two distinct groups: an intervention group that will utilize the ABCC tool and a control group that will adhere to the regular care regimen. Since the ABCC tool has not yet been integrated into South Tyrolean healthcare, theoretically, all general practitioners could participate in both intervention and control groups. Following the PRECIS-2 framework, details of the trial components are provided as a supplementary material (Additional file 1) to the manuscript, including setting, participant recruitment, intervention delivery, follow-up, and outcomes as defined by Loudon et al. [11].

To mitigate potential contamination bias—whereby patients in the control group could inadvertently receive the intervention (or vice versa) due to overlapping care by health care providers—the randomization of the intervention will be performed at the level of general practices [12]. In South Tyrol, general practitioners (GPs) work either independently in their private practices or in group practices. However, even within group practices, GPs work independently, each with their own designated patient lists provided by the public health service.

Outcomes will be monitored and evaluated 18 months after implementing the ABCC tool in the intervention group, and these results will be compared with those of the control group receiving usual care. This study aims to assess the comparative effectiveness and cost-effectiveness of the ABCC tool compared to standard care for patients with chronic diseases in South Tyrol’s general practice setting.

## Methods: participants, interventions and outcomes

### Study setting {9}

The Health Authority of South Tyrol, a region with a mix of Italian and Austrian cultures, is essentially part of the Italian National Health Service (NHS). In this region, general practices are predominantly independent entities, often run by single practitioners or small groups of GPs who work independently but may share office space. These practices are not typically housed within hospitals or larger medical centers, maintaining a focus on community-based care. Patients are assigned to GPs by the public health service, and GPs are paid on a per capita basis for the number of patients assigned. This study will be conducted in primary care facilities in South Tyrol. Data will be collected from patients in the general practice in this region. Researchers will enroll in general practices with participation from healthcare providers, such as general practitioners and practice nurses. Practice randomization will be stratified. Subsequently, healthcare providers will recruit the patients. This is because both the provider and the patient will either use the ABCC tool (intervention group) or receive standard care (control group). The study outcomes are assessed at the practice and patient levels.

### Eligibility criteria {10}

Eligibility criteria include patients with a diagnosis of chronic obstructive pulmonary disease (COPD), asthma, type 2 diabetes mellitus (T2DM), and/or heart failure, who are 18 years of age or older, and who understand and read German or Italian. Exclusion criteria include patients with asthma or COPD who had taken prednisone for an exacerbation within 6 weeks prior to the start of the study and patients with T2DM or heart failure who had been hospitalized within 6 weeks prior to the start of the study.

Eligibility criteria for participants will be validated through manual chart review, owing to the variability in software programs used across general practices and the lack of a unified EHR system in the region.

### Who will take informed consent? {26a}

Informed consent will be obtained by either the General Practitioner (GP) investigator or the General Practice Assistant involved in the study. These individuals will be comprehensively trained on how to obtain their informed consent. This training emphasizes the importance of transparency and open communication during the consent process, the need to respect participant autonomy, and the need to ensure that participants fully understand the study’s implications.

The consent process will involve potential participants who have received an informed consent form approved by the Ethics Committee. This form contains detailed information about the trial, including its purpose, duration, procedures, and associated risks and benefits. Participants will be given the opportunity to read this document alone or with the GP investigator or a General Practice Assistant.

They will be able to ask any questions they may have about the trial and the GP investigator or General Practice Assistant will provide comprehensive answers to these queries. Once the participants are comfortable and have confirmed their understanding of the study, they will be asked to provide written consent to participate. This procedure ensures that the consent obtained is informed, voluntary, and in accordance with the guidelines.

### Additional consent provisions for collection and use of participant data and biological specimens {26b}

This study requires the collection and use of the participant data. As part of the informed consent process, participants will be informed about the data collection procedures, the type of data that will be collected, how they will be used, and how their privacy will be protected.

Participants will be asked for their consent by the research team to use their anonymized data for the purposes of this study. They will also be informed that their participation is voluntary and that they have the right to withdraw their consent at any stage of the study without any negative implications for their care.

The consent form contains provisions for any potential ancillary study that may arise from the primary study. If such ancillary studies involve additional data collection or usage, separate consent will be sought from participants at that time. This approach ensures that the participants were fully aware of how their data would be used, providing them with control over their personal information.

## Interventions

### Explanation for the choice of comparators {6b}

The comparator in this study is the current standard of care for managing COPD, asthma, T2DM, and heart failure. Current standard of care follows integrated care protocols developed by interprofessional groups that include disease diagnosis, monitoring, and treatment pathways. However, these protocols do not include the use of patient-reported outcome tools, which the study intervention seeks to integrate for a more comprehensive assessment of patient health outcomes. Comparing the ABCC tool with the current standard of care allows us to evaluate its added value and efficacy in a real-world setting. If the ABCC tool proves to be superior or equivalent to the current standard of care, it would provide a compelling argument for its integration into routine clinical practice. The use of the current standard of care as a comparator ensured that all study participants received a level of care aligned with the best current practices. This approach respects ethical considerations by ensuring that no participant is deprived of a known effective treatment. By comparing outcomes, resource utilization, and costs between the intervention and the current standard of care, we can gain insights into the potential benefits and impacts of the wide-scale implementation of the ABCC tool.

### Intervention description {11a}

This study involves the use of the ABCC tool. This tool is a patient-reported outcome measure (PROM) designed to assist in individualized medical decision-making within a complex and changing healthcare environment. The ABCC tool is an evolution of the Assessment of Burden of COPD (ABC) tool developed in 2014 [13] and has been expanded to cover various chronic conditions beyond COPD, including asthma, type 2 diabetes mellitus (T2DM), heart failure [6], and post-COVID syndrome [8].

The ABCC tool integrates a generic module with disease-specific modules to facilitate a comprehensive approach to patient care. Table 1 lists the four key components, their explanations, and illustrative descriptions to provide insight into how each component supports patient-centered care during the consultation.

**Table 1 Tab1:** Components of the ABCC Tool in consultation sessions

**Component**	**Explanation**	**Illustrative description**
Assessment	Utilizes a short scale to assess the burden of disease due to one or more chronic conditions	Questionnaire
Visualization (balloon diagram)	Self-assessment results are visualized using balloons of varying colors and heights to represent scores for items or domains. Green for good scores, red for areas of difficulty, and gray for previous scores to indicate change	Imagine a balloon for each health domain: green balloons rise high for areas of well-being, while red balloons hover low for challenges
Shared decision-making discussion	A discussion between the patient and healthcare provider, supported by treatment recommendations integrated into the tool	Guided conversation on treatment options based on assessment results
Agreement with personalized care targets	Setting individualized care goals based on the patient’s self-assessment and shared decision-making discussions	A section within the tool where patients and providers document agreed-upon health goals

The ABCC tool uses the ABCC scale, which includes general, disease-specific, and lifestyle questions to assess a patient’s disease burden. Access to participant responses and balloon visualizations is provided through an online portal, accessible on both tablet PCs for patient surveys and GP office desktop PCs, with the option for printing to facilitate in-depth discussions during consultations.

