### Outcomes {12}

#### Primary outcome

The primary objective of this study is to assess changes in perceived quality of care over an 18-month period using the Patient Assessment of Chronic Illness Care (PACIC) [20, 21] as the comparative measure. This assessment will be administered at baseline and then at specified follow-up points to determine changes from usual care in the cohort of participants.

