## Assignment of interventions: allocation

### Sequence generation {16a}

In this cluster-randomized trial, general practices throughout South Tyrol serve as the unit of randomization. After recruitment, these practices will be assigned to either the intervention or control group through a stratified randomization process. Stratification factors include the patients’ preferred language (Italian or German), the location of the practice (urban or rural), and the demographic characteristics of the general practitioners (sex and age). Sequences will be generated using computer software to pre-generate random assignments. Practices in the intervention group will use the ABCC tool via a provided tablet PC, while those in the control group will continue their usual care without access to the tool.

To maintain the integrity of this randomization process and control for potential confounding, these stratifying variables will be explicitly included in the analytical models.

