## Data collection and management

### Plans for assessment and collection of outcomes {18a}

The assessment and collection of outcomes will be performed by using well-established survey instruments. These include the Patient Assessment of Chronic Illness Care (PACIC) as the primary outcome, that is, perceived quality of care. Secondary outcomes such as health-related quality of life, patient activation, and capability well-being will be assessed using EQ-5D-5L and Patient Activation Measure (PAM), respectively. Data collection will follow a set schedule with checkpoints at 6-, 12-, and 18-month intervals from the start of the intervention to monitor changes in these outcomes over time.

The research team will facilitate survey completion through telephone or email contact, offering participants the option to complete surveys online or on paper. In addition, participants visiting their primary care physician’s office will have the option of using the ABCC tablet to complete the survey during their visit.

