### Data management {19}

A robust data management plan is in place to store, organize, and access the collected data. We will use a secure, centralized data management system for these purposes, and only authorized study personnel will have access to it [28]. In addition, regular data audits will be conducted to identify and correct any data entry errors or inconsistencies, thereby ensuring data integrity.

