Third, ensuring participant adherence to the study protocol, particularly with respect to completing the questionnaires at the required time points, is another operational challenge [35]. Strategies to promote participant retention and to manage missing data were incorporated into the study design.

Finally, the study relies on self-reported outcome measures, which could introduce bias [36]. Efforts have been made to select reliable and validated instruments, and the statistical analysis plan includes strategies for adjusting for potential confounding factors. Although these issues pose challenges, they have been carefully considered in the study design and management plan to reinforce the robustness and reliability of the results.

Although the use of tablets and the Curavista App for data collection and management in the ABCC study can provide several benefits, such as real-time data access, streamlined data entry, and improved patient engagement, it also introduces a few potential challenges that need to be addressed [37]. One of the main challenges is the integration of the Curavista App with various software systems employed in various general applications. Ensuring seamless data exchange and synchronization between these systems and their applications is essential for maintaining the data integrity and usability. Moreover, mapping patient data from the app to the corresponding patient charts and dossiers might require custom solutions, considering the diverse formats and structures of electronic health records across practices. Furthermore, the use of tablets for patient-reported outcome measures might present issues related to digital literacy among patients, especially among the elderly or those unfamiliar with such technology [38]. This could affect the quality and completeness of the collected data.

Another concern is data privacy and security, particularly given the use of the Dutch data platform in a study conducted in South Tyrol. The Curavista App is a certified EU data platform, ensuring compliance with different national and regional data protection regulations will be paramount [39, 40]. Clear communication regarding data handling and privacy safeguards is crucial for maintaining participants’ trust and cooperation.

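### Patients may enter PACIC, their rating of care, on the ABCC tablet, a GP-facing device only intervention practices hold; nothing tells them the GP cannot see those answers

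*Protocol article*

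**What the plan says.** All references are to the Protocol article.

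- **What is rated.** Under Primary outcome, the measure is perceived quality of care over 18 months, by PACIC.
- **How it is collected.** Plans for assessment and collection of outcomes {18a} has the research team contact participants by telephone or email, "offering participants the option to complete surveys online or on paper". It then adds that participants attending their doctor's office "will have the option of using the ABCC tablet to complete the survey during their visit". In context the survey is PACIC, EQ-5D-5L and PAM.
- **Who has the tablet.** Sequence generation {16a}: "Practices in the intervention group will use the ABCC tool via a provided tablet PC"; control practices have no access to the tool.
- **What the tablet does with answers to the tool.** Intervention description {11a}: "The ABCC tool uses the ABCC scale, which includes general, disease-specific, and lifestyle questions". The next sentence says of access: "participant responses and balloon visualizations is provided through an online portal, accessible on both tablet PCs for patient surveys and GP office desktop PCs". Printing is possible, for use in consultations. The Discussion adds that the GP reviews the results with the patient immediately.
- **Who may see study data.** Data management {19} describes a secure central system and says that "only authorized study personnel will have access to it". Confidentiality {27} separates identifiers from study data and restricts personal information to essential personnel. Neither names the GP as included or excluded. Who will take informed consent? {26a} refers to a GP investigator.

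**The concern.** PACIC asks patients to judge the care they receive, which here is largely care from their own GP. A patient who believes that the GP will read the answers may well answer more kindly. The belief is enough; the GP need not look.

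The article offers, as one entry route for this rating, the device on which intervention patients have learned that their answers go straight to the GP for discussion. Control patients have no such device. A courtesy effect of this kind would therefore fall on one arm and favour the tool. Patients and GPs are unblinded, and the Discussion itself accepts that the outcomes depend on patients' perceptions. Blinding assessors and analysts does not touch the problem, and neither randomization nor covariate adjustment removes a measurement difference tied to the arm.

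**Working it through.** **Step 1. Reading the sections together**

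| Link | Where | Status |
|---|---|---|
| PACIC is the patient's rating of care | Primary outcome | Stated |
| PACIC may be completed on the ABCC tablet in the practice | {18a} | Stated, as an option |
| Only intervention practices have the tablet | {16a} | Stated |
| ABCC answers are open to the GP and discussed at once | {11a}, Discussion | Stated |
| PACIC answers are open to the GP | none | Not stated |
| PACIC answers are closed to the GP | {19}, {27} | Not expressly stated |
| Patients are told whether the GP can see PACIC answers | {26b} promises information on data use and privacy in general | Not stated for this point |

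The first four links support a risk through what intervention patients expect. The fifth, actual disclosure, is not established. The last two show that the text does not remove the expectation.

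**Step 2. The plan's own figures** (Sample size {14})

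Effect size: 0.49 / 0.96 = 0.51. An independent t-test at two-sided 0.05 and 90% power gives 81.8, so 82 per group. Inflation: 82 × 1.45 / 0.9 / 0.75 = 176.1, so 177. Both stated figures reproduce, and this point does not change them.

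**Step 3. Illustration of scale**

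The documents give neither the share of patients who would use the tablet nor any courtesy shift. Both are assumed below, only to show what would follow.

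- Bias = share of intervention patients using the tablet × shift in PACIC points.
- Effective patients per group = 180 × 0.75 × 0.9 / 1.45 = 83.8.
- Standard error of the difference = 0.96 × √(2 / 83.8) = 0.148.
- Chance of a significant result with no true effect = Φ(bias/SE − 1.96) + Φ(−bias/SE − 1.96).

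| Assumed share | Assumed shift | Bias | Bias / 0.49 | Chance of a false positive |
|---|---|---|---|---|
| 20% | 0.1 | 0.02 | 4% | about 5% |
| 50% | 0.2 | 0.10 | 20% | about 10% |
| 50% | 0.3 | 0.15 | 31% | about 17% |
| 100% | 0.3 | 0.30 | 61% | about 52% |

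The spread, from negligible to serious, comes wholly from the assumptions. The table is not an estimate for this trial.

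**The case against.** The strongest reply is that the portal sentence in {11a} is about the tool. It directly follows the description of the ABCC scale, pairs responses with the balloon diagram, and sits in a section that never mentions PACIC, EQ-5D-5L or PAM. {18a} names a device, not a data route: a tablet can open a separate research form, and the main route is online or paper completion arranged by the research team. Data management {19} and Confidentiality {27} do limit access. Which user can open which form is detail that an article often leaves to a data management plan.

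Most of this stands. A reader might infer that PACIC answers are held in the portal and that the GP reads them. The documents do not support that. Nor do they support the inference that PACIC answers will be copied into charts: the Discussion raises "mapping patient data from the app to the corresponding patient charts and dossiers" only as something that might need custom solutions, without mentioning the outcome surveys. The reference to a GP investigator in {26a} concerns who takes consent and grants no database access.

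What the reply does not meet is the choice that {18a} itself makes. It offers the intervention's own GP-facing device as an entry route for an unblinded, subjective primary outcome. A separate form behind the same screen does not help if the patient does not know that it is separate.

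**Conclusion.** The point holds as a risk, not as a demonstrated flaw. Intervention patients who complete PACIC on the ABCC tablet can reasonably expect their GP to see the rating, control patients have no equivalent device, and the text neither rules this out nor says that patients will be told otherwise. Any resulting bias would probably favour the tool on the primary outcome.

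Two assumptions carry this conclusion: that some intervention patients take up the tablet option, and that expecting the GP to read the answers makes ratings more favourable. The documents quantify neither, so the size of the bias cannot be estimated from them. It does not depend on GPs actually having access, and the documents do not show that they do. The right label is a cheap improvement.

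**What to change.** In Plans for assessment and collection of outcomes {18a}, state that PACIC, EQ-5D-5L and PAM answers, on whatever device they are given, go to a research-only form outside the ABCC portal, and that GPs and practice staff in either arm cannot open it. Tell patients in both arms this before they answer. Leave GP access to ABCC-scale responses as it is, since the intervention depends on it.

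The cost is a small set-up task, a sentence in the protocol and one in the patient information, passed through the article's own amendment route. Trial status says that recruitment had not begun, so no data already collected would be affected. If the separation is already intended, only the wording and the notice to patients are needed.
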